## 8.3 Monitoring

The research will be monitored by the Haga Hospital's monitor pool according to the Haga Hospital's monitoring plan.

## 8. Statistical analysis

### 8.1. Descriptive statistics

This study will contain different types of data. Both qualitative data and quantitative data are used. The measurements are made using four measuring scales: ordinal, nominal, interval and ratio. Which scale is used depends on the variable.

The following patient characteristics will be stored in the database which will be analyzed later:

- Date of birth
- Comorbidities
- Medication use
- Smoking / not smoking
- Head complaint (Sore throat with fever, sore throat without fever, dysphagia, detritus, halitosis, OSAS)
- Presence of other complaints (Sore throat with fever, sore throat without fever, dysphagia, detritus, halitosis, OSAS)
- Number of antibiotics used in the past year in connection with tonsil-related complaint
- Number of days of absenteeism from work / school related to tonsil-related complaints
- VAS score with regard to complaints (to be completed per complaint)
- Friedman classification (see appendix 1)

**The variables that are analyzed related to the procedure are the following:**

#### ***Laser procedure:***

- Duration of the laser procedure
- Total duration of outpatient visit
- Amount of local anesthesia administered (number of cc)
- Pain during the procedure, VAS score (perception pt). Reduce pain score 30 minutes after surgery, 1 day after surgery, 2 weeks after surgery.
- Use of additional anesthetic (number of cc)
- Coagulation required / not required during procedure
- Complications during surgery

#### ***Classic TE procedure:***

- Duration of hospitalization
- Pain relief administered during surgery (medication, dosage)
- Pain related to procedure, VAS score (patient perception). Pain score decrease 2 weeks after surgery.
- Complications during surgery

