**Outcome measures:**

The results will be based on the following outcome measures: number of days postoperative recovery to resumption of daily activities, presence or absence of preoperative tonsil-related complaints, postoperative pain scores and analgesia use, procedure-related complications and patient satisfaction.

**Risks and complications:** For the number of clinic visits, measurement moments and actions, see the flow chart in chapter 3.

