##### 3.1.2. Secondary outcome measures

- Presence or absence of the tonsil related complaint
- Number of episodes of tonsillitis per year objectified by the general practitioner or ENT specialist
- Number of antibiotics courses for tonsillitis each year
- Average number of days per year of sick leave due to tonsil-related complaints
- Presence / absence of halitosis
- Presence / absence of detritus
- Pain complaints during / after the procedure
- Complications
- Patient satisfaction with regard to the procedure and reduction of complaints (using VAS)
- Time to return to work / school resumption
- Number of days of sick leave in the year after surgery (second follow-up study)
- Cost Effectiveness laser tonsillotomy vs classic tonsillectomy (second follow-up study)
- Budget Impact laser tonsillotomy vs classic tonsillectomy (second follow-up study)

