### 7.5. Study procedure

To evaluate the primary and secondary outcome measures, the patient will be asked to complete a digital evaluation form preoperatively, 2 weeks, 6 months, 1 year and 2 years after the procedure (follow-up study). These forms will be offered by e-mail. In the event of recurrent complaints after the procedure, the patient is asked to go to the ENT doctor /

general practitioner for assessment and to report this to the investigator (by telephone / email). This will also be re-evaluated in the fixed measurement moments.

The operator will fill in a number of questions related to the procedure.

Laser procedure:

- Duration of the laser procedure
- Total duration of outpatient visit
- Amount of local anesthesia administered (number of cartridges)
- Pain during the procedure (VAS score) (patient perception)
- Use of supplemental anesthetic, and the amount thereof
- Coagulation required / not required during procedure
- Complications during surgery

Classic TE procedure:

- Duration procedure (cutting time)
- Duration of hospitalization
- Pain relief administered during surgery (medication, dosage)
- Pain related to procedure (injecting an IV, etc.) (VAS score) (perception pt)
- Coagulation required / not required during procedure
- Complications during surgery

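### Section 8.1 lists different pain scores and times for the two arms, so early VAS pain has no listed control measurement and the procedural scores are not comparable

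*Protocol*

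**What the plan says.** Pain is a single secondary outcome for the whole trial: "Pain complaints during / after the procedure" (Protocol 3.1.2, repeated in 7.2). The summary in section 1 also names "postoperative pain scores and analgesia use, procedure-related complications and patient satisfaction" among the outcome measures. Section 8.2 compares continuous secondary outcomes between arms by an unpaired t-test or a Mann-Whitney U test, at a two-sided 0.05 level.

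The variables are then listed arm by arm in section 8.1:

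- Laser: "Pain during the procedure, VAS score (perception pt). Reduce pain score 30 minutes after surgery, 1 day after surgery, 2 weeks after surgery".
- Classic tonsillectomy: "Pain related to procedure, VAS score (patient perception). Pain score decrease 2 weeks after surgery".

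Section 7.5 says what the operator's form records about the procedure. For laser it is "Pain during the procedure (VAS score) (patient perception". For tonsillectomy it is "Pain related to procedure (injecting an IV, etc.) (VAS score) (perception pt". Section 7.5 also asks every patient to "complete a digital evaluation form preoperatively, 2 weeks, 6 months, 1 year and 2 years after the procedure (follow-up study".

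**The concern.** A between-arm test needs the same question, asked at the same time, in both groups. The pain lists in 8.1 meet that condition at only one post-procedure time. Less pain is part of the rationale for the laser technique in section 2, and section 3 hypothesises significantly better secondary outcomes. If the lists are followed as written, the VAS scores closest to surgery, where a difference in pain would be expected, exist only in the laser arm and can only be described.

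The procedural score carries a second risk. Both arms have a VAS with a similar name, so the general rule in 8.2 could be applied to it, although the two scores rate different experiences. The direction of the resulting bias is unknown, and it could make the laser look more painful as easily as less. No analysis plan can repair this later, because scores that were not collected cannot be recovered.

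**Working it through.** No formula applies to the point itself. The check sets the lists side by side.

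| Pain score | Laser (8.1, 7.5) | Classic tonsillectomy (8.1, 7.5) | Comparable? |
|---|---|---|---|
| Procedural VAS | Pain during the laser treatment | Procedure-related pain, with IV insertion as the example | No, different stimuli |
| 30 minutes | Listed | Not listed | No control score |
| 1 day | Listed | Not listed | No control score |
| 2 weeks | Listed | Listed | Yes, as an absolute score |

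1. **Count.** The laser arm has 4 pain moments (procedure, 30 minutes, 1 day, 2 weeks) and the tonsillectomy arm has 2 (procedure, 2 weeks). Of the 3 post-procedure times, 3 − 1 = 2 have no listed counterpart.

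2. **Stimulus.** Laser patients are awake under local infiltration (6.1) and rate the treatment of the tonsil. Tonsillectomy patients are intubated under general anesthesia (6.2), so their procedural score cannot rate the tonsil surgery while it happens. Section 7.5 confirms this by giving IV insertion as its example.

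3. **Does the common form schedule fill the gap?** The e-mailed forms in 7.5 fall before surgery and at 2 weeks, 6 months, 1 year and 2 years. They support the 2-week comparison, but none falls at 30 minutes or day 1.

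4. **The 2-week score.** 8.1 speaks of a reduced or decreased score, which may be a translation artefact for a score simply being taken. Read as an absolute VAS, the 2-week score can be compared. If a change from the procedural score is meant, it cannot, because the starting points differ. The protocol does not say what the decrease is measured from.

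5. **What is unaffected.** The days of painkiller use are listed in 8.1 without distinction by arm and compared by survival analysis in 8.2. The primary endpoint does not use the VAS. Its power figure in 7.4 (80.2%) reproduces. With exponential times and medians of 8 and 13.5 days, the 14-day event probabilities are 1 − exp(−ln2 × 14/8) = 0.703 and 1 − exp(−ln2 × 14/13.5) = 0.513. That gives 95 × (0.703 + 0.513) = 115.5 events. The hazard ratio is 8/13.5 = 0.593, and Schoenfeld's formula then gives 80.3%.

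**The case against.** The strongest reply is that the schedule has not been fully seen. Section 1 refers the reader to the flow chart for measurement moments, and that figure is not available here. This stands. A reader might infer that no tonsillectomy patient will give an early pain score, or that the laser day-1 score has no collection point at all. The documents do not support either as a flat statement, because 7.5 does not say that its forms are the only contacts. What remains is that the written lists in 8.1 differ by arm, and the figure would not remove that difference.

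Second, pain in the control arm is not left without data. Besides painkiller use, 8.1 lists complaints after surgery with a VAS for both arms, although without a time. This also stands, and the gap is confined to the early VAS scores.

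Third, different procedural scores are partly unavoidable when one operation is done under general anesthesia. The lists stand under descriptive statistics, and no sentence explicitly tests one procedural score against the other. That is fair, since such a test follows only from the general rule in 8.2. It would also be too strong to call the tonsillectomy item a needle-stick score, because 7.5 leaves the item open beyond IV insertion. The two items are nevertheless not the same measurement, and the plan should say that they will not be tested against each other.

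Fourth, pain is one of 13 listed secondary outcomes, and the hypothesis in section 3 does not name it. That limits the weight of the point but does not remove it.

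**Conclusion.** The point holds as a mismatch between the arm-specific lists in 8.1 for an outcome that 3.1.2 and 7.2 define once for both arms. Two of three post-procedure VAS times have no listed control measurement, and the procedural VAS is not comparable. The 2-week absolute VAS and the duration of painkiller use can still be compared, and the primary analysis is untouched. It should be corrected, but it does not threaten the trial's main conclusion.

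This rests on the written text alone, with the flow chart unchecked, and on the 2-week question being the same in both arms. It might be tempting to size the loss with the 70% of laser and 51% of tonsillectomy patients expected to have recovered by day 14. Those figures describe resumption of activities under an assumed exponential form, not pain, and they do not measure this problem.

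**What to change.** - In 8.1, list one postoperative throat-pain VAS question for both arms at the same times, at least day 1 and 2 weeks. State that the score is an absolute value, or name the baseline if a change is meant.
- Make 7.5 and the flow chart agree with that list, including the day-1 form.
- Test between arms only on these common scores.
- Report laser intra-procedural pain and tonsillectomy procedure-related pain descriptively, within arm.
- A score at about 30 minutes may be kept, but it should be read with caution because residual anesthesia differs between the arms.

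The cost is one added day-1 e-form item in both arms and a small amendment to the protocol and CRF. No extra staff or procedure is needed, and no treatment changes.

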**The variables to assess effectiveness and patient satisfaction include the following:**

- Presence / absence of the complaints for which the intervention was undergone
- Duration of recovery period (time to return to work / resumption of daily activities) in days
- Duration of use of painkillers in number of days
- Satisfaction with the procedure (VAS score)
- Complaints after surgery (on / absent, VAS score)
- Short and long term complications (bleeding, infection, abscess)
- Number of laser sessions required
- If patient eventually underwent classic tonsillectomy
- Number of antibiotics used in the period after surgery in connection with tonsil-related complaint
- Number of days of absenteeism from work / school related to tonsil-related complaints after the procedure
- The patient would / would not recommend the procedure to others

## 8.2. Analysis

All analyzes will be performed with an intention-to-treat analysis.

A two sided p value  $<0.05$  will be considered significant for all analyses. Survival analysis will be used to compare the primary outcome of recovery time. Survival analysis will also be used to compare time to return to work and postoperative analgesic use. Secondary outcome measures on a continuous scale will be compared using unpaired T-tests or Mann-Whitney U tests, depending on the normality of data (tested using Shapiro-Wilk test). Proportions will be compared using Fisher exact tests.

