**Complications of laser treatment:**

- About 10% have not gotten rid of the complaints and have so many complaints that they undergo a classic dissection tonsillectomy
- In total, about 20% of patients undergo more than 1 laser treatment
- wound infection (3.4%)
- Bleeding requiring intervention (<1%)
- Allergic reaction to the local anesthetic (<1%)
- Side effects of the anesthetic (xylocaine 2% / adrenaline 1: 80,000) as described in the package insert (<1%)

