In a period of four and a half years, 425 patients with chronic recurrent tonsillitis, fetor ex ore, swallowing complaints or obstructive complaints due to tonsil hypertrophy underwent a CO2 laser tonsillotomy after informed consent. This showed that patients were able to resume their daily activities and work after an average of 4.2 days. Of the 204 patients who could be followed for a long time (mean 16.8 months, range 1-40) it turned out that 69.6% eventually became completely free of complaints, in 19.1% there was such a reduction in complaints that no further intervention was desired, 10.3% were not free of symptoms after treatment and underwent a classic tonsillectomy. In 2.6% there was minimal bleeding which could be treated conservatively. In 8.6% antibiotics were prescribed shortly after the procedure, but these figures do not fully correspond to reality. In the early years, the GP regularly prescribed antibiotics because of the white discoloration of the wound bed. After better information provision, this number has decreased significantly. In 2010, 117 patients were treated with the laser and antibiotics were prescribed for a wound infection in 4 patients (3.4%). Two patients had a severe vagal reaction to the local anesthetic, causing the procedure to be prematurely discontinued.

A comparison with the classic tonsillectomy was not made in this study. Because of the expected potential of the CO2 laser tonsillotomy, we feel the need to perform a thorough comparative study with the classic tonsillectomy. The aim of this study is to provide more insight into postoperative recovery, effectiveness, complications (both in the short and longer term) and patient satisfaction after CO2 laser tonsillotomy compared to a classic tonsillotomy.

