### 3. Aim of the study

The aim of this study is to compare the effectiveness of CO2 laser tonsillotomy in a selected group of patients with a classic tonsillectomy. It is hypothesized that the number of days postoperative recovery after the laser procedure differs for at least 3 days from the classic tonsillectomy, that the effectiveness of the CO2 laser tonsillotomy does not differ by more than 30% from the classic tonsillectomy and there are significantly better secondary outcomes.

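### Complaint status is compared by randomised arm with no rule for laser patients who later have a classic tonsillectomy, so cures by the control operation count towards laser

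*Protocol*

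**What the plan says.** Section 3 of the protocol asks how effective laser tonsillotomy is against classic tonsillectomy and hypothesises "that the effectiveness of the CO2 laser tonsillotomy does not differ by more than 30% from the classic tonsillectomy". Section 8.1 lists the effectiveness variables, the first of which is "Presence / absence of the complaints for which the intervention was undergone". Section 7.5 collects patient forms at 2 weeks, 6 months, 1 year and 2 years. Section 8.2 sets the principle, "All analyzes will be performed with an intention-to-treat analysis", and the test for proportions, Fisher's exact test at a two-sided 0.05.

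The protocol also expects failures of laser to move to the control operation. The Summary, under complications of laser treatment, says: "About 10% have not gotten rid of the complaints and have so many complaints that they undergo a classic dissection tonsillectomy". The Introduction reports from the group's earlier series that "69.6% eventually became completely free of complaints", that "in 19.1% there was such a reduction in complaints that no further intervention was desired", and that "10.3% were not free of symptoms after treatment and underwent a classic tonsillectomy".

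Conversion is recorded: section 8.1 lists "If patient eventually underwent classic tonsillectomy" as a separate effectiveness variable. No section says how complaint status after that operation enters the comparison of complaint presence.

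**The concern.** Three provisions act together: a yes/no complaint endpoint read at fixed visits, analysis by randomised arm, and silence on later tonsillectomy. A laser patient whose complaint persists, who then has the control operation and is well at the next visit, is recorded as complaint absent in the laser arm. The traffic runs essentially one way, because a patient whose tonsils have been removed cannot convert to laser.

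Section 3 asks about laser compared with tonsillectomy, not about a strategy that includes tonsillectomy. For that question, each cure by the second operation moves the arms together. The more often laser fails and is followed by tonsillectomy, the more alike the arms look. A non-significant Fisher test could then be taken as support for similar effectiveness when part of the similarity came from the control treatment. The laser rate would also not be comparable with the 69.6% in the Introduction, because the earlier series kept converters in a category of their own.

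**Working it through.** **The plan's own figure.** The only power stated is for the primary endpoint (section 7.4): 80.2% with 95 per arm, medians of 8 and 13.5 days, and 14 days of observation. Assuming exponential recovery times, the hazard ratio is 8/13.5 = 0.593. The probabilities of recovery by day 14 are 0.703 (laser) and 0.513 (tonsillectomy), so 95 × (0.703 + 0.513) ≈ 115.5 events are expected. Schoenfeld's formula then gives 80.3%. The stated figure reproduces, and the present point does not touch it. No power is stated for complaint status.

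**Inputs**
- Complaint-free after laser: 0.696 (Introduction, 204 patients followed long term).
- Converted to classic tonsillectomy: 0.103 (Introduction; the Summary says about 10%). Of 95 laser patients this is 0.103 × 95 ≈ 10.
- Patients per arm: 95 (section 7.4).
- Complaint-free rate after tonsillectomy, p_TE: not in the protocol. Assumed, and shown from 80% to 99%.
- Cure rate among converters, c: not in the protocol. Assumed equal to p_TE in the table below.
- The 19.1% with reduced complaints count as complaint present, which is the strict reading of a presence/absence endpoint.

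**Step 1. Laser rate under the two scorings**
- Conversion counted as failure: 0.696.
- Complaint status as observed at follow-up: 0.696 + 0.103 × c.
  - c = 0.50: 0.696 + 0.0515 = 0.7475
  - c = 0.90: 0.696 + 0.0927 = 0.7887
  - c = 1.00: 0.696 + 0.1030 = 0.7990

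The shift is 0.103 × c: about 5 points at c = 0.50 and 10.3 points at most.

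**Step 2. Difference and Fisher power.** The difference is p_TE minus the laser rate. Power is the exact probability, summed over two independent binomials of 95, that the two-sided Fisher p-value is below 0.05.

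| Assumed p_TE | Laser rate as observed | Difference, conversion = failure | Difference, as observed | Fisher power, conversion = failure | Fisher power, as observed |
|---|---|---|---|---|---|
| 80% | 77.8% | 10.4 | 2.2 | 32% | 5% |
| 85% | 78.4% | 15.4 | 6.6 | 67% | 17% |
| 90% | 78.9% | 20.4 | 11.1 | 93% | 50% |
| 95% | 79.4% | 25.4 | 15.6 | 99.8% | 88% |
| 99% | 79.8% | 29.4 | 19.2 | >99.9% | 99.8% |

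Example, p_TE = 90%: 0.90 − 0.696 = 0.204, against 0.90 − 0.7887 = 0.1113.

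**Step 3. Dependence on the 19.1%.** If patients with reduced complaints count as successes, the laser rate with conversion as failure is 0.696 + 0.191 = 0.887. At p_TE = 95% the difference is 6.3 points, with an expected 95% limit of about 14 points against laser. The shift from scoring is still 0.103 × c, but a 30-point reading would be satisfied under either scoring.

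**The case against.** The strongest reply is that intention-to-treat fixes who is compared, not how a converted patient is scored. Counting conversion as failure is fully compatible with section 8.2. That stands: the weak point is the endpoint definition. A reader might infer that intention-to-treat is the wrong principle here. The protocol does not support that, and the remedy keeps it.

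Second, complaint status by assignment is a valid estimate for a policy of laser first and tonsillectomy if needed. That also stands, but section 3 asks about laser itself, so the policy result belongs in second place.

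Third, failures are not hidden. Conversion and number of laser sessions are listed as effectiveness variables, and the earlier series reported converters apart. This lowers the severity. It does not put conversion into the complaint comparison.

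Fourth, a scoring rule might be left to a statistical analysis plan. Detail can be, but the protocol already fixes the endpoint, the visits, the principle and the test, and following them gives a diluted answer to its own question.

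A stronger claim is tempting: that the 30% margin would be met falsely. With p_TE at 95%, the chance that a 95% confidence interval stays within 30 points is 14% with conversion as failure and 86% as observed. The protocol does not bear that reading out. Section 8.2 plans no test against a margin, and section 3 does not say whether 30% is absolute or relative. In every row of the table the difference with conversion as failure lies inside 30 points, so the 86% is not a false-claim rate. The contrast also depends on an assumed tonsillectomy rate and on scoring the 19.1% as failures.

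**Conclusion.** The point holds for the secondary complaint endpoint. Applied as written, the plan credits laser with cures by the control operation and pulls the comparison towards no difference by up to 10.3 points. At an assumed 90% complaint-free after tonsillectomy, with converters cured at the same rate, that roughly halves the observed difference and cuts the power of the planned Fisher test from about 93% to 50%.

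The direction does not depend on the assumptions, but the size does. It rests on a tonsillectomy rate and a converter cure rate that the protocol does not give. It also rests on rates from 204 of 425 patients in an uncontrolled series, and on the strict reading of complaint presence. The 10.3% accrued over a mean of 16.8 months, so the effect at 6 months is probably smaller.

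The primary recovery endpoint, its sample size and its power are not affected. This should be fixed, but it is not a condition for the trial to stand.

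**What to change.** Keep intention-to-treat, with every patient in the randomised arm. For the section 3 effectiveness question, define failure at each assessment time as either of:
- the complaint is present; or
- the patient has by then converted to classic tonsillectomy (in the tonsillectomy arm, had further tonsil surgery).

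Report complaint status as observed, by randomised arm, as a supportive analysis labelled as the laser-first strategy. A sensitivity analysis that also counts repeat laser sessions as failure would show how far the result depends on retreatment. State whether patients with reduced complaints count as complaint present, since the size of the result depends on it.

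The cost is wording. Conversion and number of laser sessions are already listed for collection, and neither sample size nor visits change. If further tonsil surgery after tonsillectomy is not already captured, one form item covers it. The price for the sponsor is a less favourable laser effectiveness figure: about 69.6% instead of up to 79.9% on the earlier series' rates.

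### Continuous secondary outcomes are compared with unadjusted tests chosen by a Shapiro-Wilk pre-test, so baseline values and the stratification factor already collected go unused and precision is lost

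*Protocol*

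**What the plan says.** Protocol section 8.2 sets one rule for continuous secondary outcomes: "Secondary outcome measures on a continuous scale will be compared using unpaired T-tests or Mann-Whitney U tests, depending on the normality of data". Normality is "tested using Shapiro-Wilk test". The other methods named there are survival analysis (recovery time, return to work, analgesic use) and, for binary outcomes, "Proportions will be compared using Fisher exact tests". The section names no covariate, regression model or count model.

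Section 8.1 lists three preoperative measures that bear on these outcomes:

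- "VAS score with regard to complaints (to be completed per complaint"
- "Number of antibiotics used in the past year in connection with tonsil-related complaint"
- "Number of days of absenteeism from work / school related to tonsil-related complaints"

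The list of effectiveness and satisfaction variables later in the same section has postoperative counterparts: "Complaints after surgery (on / absent, VAS score", "Number of antibiotics used in the period after surgery in connection with tonsil-related complaint", and absence days after the procedure. Section 7.5 provides a preoperative form and forms at 2 weeks, 6 months, 1 year and 2 years. Section 7.3 stratifies randomisation by indication.

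**The concern.** Two features of the stated rule are weak.

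First, the tests take no account of a patient's own baseline value, or of the indication used to stratify the randomisation. Both plausibly predict the outcome. A patient enrolled for recurrent tonsillitis and one enrolled for halitosis would be expected to differ in antibiotic use whichever operation they receive. Leaving such predictors out widens the confidence interval and lets a chance baseline difference pass into the observed contrast.

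Second, the choice between a mean comparison and a rank comparison is made from the outcome data. The quantity being compared is therefore not fixed in advance, and it could differ between time points for the same variable.

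Section 3 expects significantly better secondary outcomes with the laser, so precision on them matters to what the trial can claim.

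**Working it through.** **The plan's own figure.** The only power stated is for the primary outcome (section 7.4): 80.2% with 95 per arm, medians of 8 and 13.5 days, and 14 days of observation. Under exponential times:

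- Hazard ratio = 8/13.5 = 0.593.
- Event probability by day 14 = 1 − exp(−ln2 × 14/median) = 0.703 (laser) and 0.513 (classic).
- Expected events = 95 × (0.703 + 0.513) = 115.5.
- Schoenfeld power = Φ(√115.5/2 × |ln 0.593| − 1.96) = 80.3%.

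The stated figure is reproduced and does not depend on the present point. No power is stated for any secondary outcome.

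**What baseline adjustment would gain.** Inputs are 95 per arm (section 7.4) and r, which the protocol does not give and which is assumed here over a range. The comparator is an unadjusted comparison of means.

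- ANCOVA variance factor = 1 − r².
- Take an effect that the unadjusted t-test detects with 80% power: standardised difference = √(2/95) × (1.960 + 0.842) = 0.406.
- ANCOVA power = Φ(2.802/√(1 − r²) − 1.960). Patients per arm for the same 80% = 95 × (1 − r²).

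| r (assumed) | Variance saved | ANCOVA power | Per arm for 80% | Unadjusted change score, power |
|---|---|---|---|---|
| 0.2 | 4% | 81.6% | 91.2 | 60% |
| 0.3 | 9% | 83.6% | 86.5 | 66% |
| 0.5 | 25% | 89.9% | 71.3 | 80% |
| 0.6 | 36% | 93.8% | 60.8 | 88% |

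The last column matters because section 8.2 does not say whether follow-up values or changes enter the test. The change score has variance factor 2(1 − r). Below r=0.5 it does worse than the follow-up value alone, and at every r shown it does worse than ANCOVA.

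**How the Shapiro-Wilk rule behaves.** Simulation with 95 per arm, 2,000 runs per scenario, t-test only if both arms pass at 0.05. The distributions are assumptions: a negative binomial count with mean 1 and dispersion 1, and a rounded VAS bounded at 0 to 10, drawn around 2 with SD 2.5.

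- Shapiro-Wilk rejected in 100% of runs in both settings, so the rule always led to Mann-Whitney.
- Type I error of the whole procedure was 4.4% (count) and 5.0% (VAS).
- Count, mean 1 against 0.5: power was 78% for Mann-Whitney and 85% for the t-test.
- VAS, centred on 2 against 3 before bounding: 74% for Mann-Whitney and 75% for the t-test.

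For outcomes of this shape the pre-test decides nothing useful. It directs the analysis to a rank test that does not itself estimate a mean difference or rate ratio.

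**The case against.** The strongest reply is that nothing here is invalid. An unadjusted comparison in a randomised trial is unbiased, chance imbalance is already covered by the significance level, and the simulated type I error is at its nominal value. If Shapiro-Wilk nearly always rejects, the choice of test is in effect fixed. All of this stands, and it limits the point to efficiency and to fixing the estimand.

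Several stronger readings are tempting, but the protocol does not support them:

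- *That counts are assigned to the t or Mann-Whitney tests.* Section 8.2 speaks of outcomes on a continuous scale. Antibiotic courses and absence days fall under that rule only by inference, because no other named method fits them.
- *That complaint VAS is a listed endpoint.* Sections 3.1.2 and 7.2 list presence or absence of complaints and a satisfaction VAS. Postoperative complaint VAS appears only among the effectiveness variables in section 8.1.
- *That baseline absence covers the prior year.* Section 8.1 gives a one-year window for antibiotics but none for absence.
- *That patients are followed for different lengths of time.* Section 7.5 sets the same forms for everyone. Withdrawal is allowed (section 7.6), so unequal observation is possible but not stated.
- *That no estimate or confidence interval will be reported.* Section 8.2 names tests and is silent on reporting.
- *That the 25% saving is what the trial forgoes.* The 1 − r² factor is measured against an unadjusted mean comparison. It does not carry over to Mann-Whitney or to a count model. The Introduction reports that 69.6% of 204 laser patients followed long term became free of complaints, and the tonsillitis indication requires more than 4 episodes a year. A floor at follow-up and a restricted baseline range both tend to lower r.

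**Conclusion.** The point holds as a loss of precision in a method that the protocol itself states. Section 8.2 fixes unadjusted tests chosen by a pre-test, while baseline values of the same measures and the stratification factor are already to hand. The size depends on r: variance falls by 4% at r=0.2, 9% at 0.3 and 25% at 0.5, or about 2, 4 and 10 points of power from a base of 80%. The lower part of that range may be the more realistic for complaint scores. No inflation of type I error is shown. Only secondary outcomes are affected; the primary survival analysis and its sample size are not.

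**What to change.** Reword the secondary-outcome part of section 8.2:

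- Drop the Shapiro-Wilk rule and name one method per outcome.
- Follow-up complaint VAS: ANCOVA with the baseline VAS for the same complaint and indication. Report the adjusted mean difference with a 95% confidence interval.
- Antibiotic courses and absence days: a count model, for example negative binomial, with the baseline count and indication as covariates and, where observation time differs between patients, a log-time offset. Report the rate ratio with a 95% confidence interval.
- Satisfaction VAS has no baseline value, and no baseline count of tonsillitis episodes is listed. Adjust these outcomes for indication only.
- Keep Mann-Whitney as a sensitivity analysis.
- State the period that the baseline absence question covers.

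This needs no new patients, visits or measurements. The cost is a revised paragraph and slightly more analysis work with standard software.
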